### Power analysis and sample size calculation

Based on our findings from the Kids-HD sample, our central hypothesis is that GE participants will demonstrate altered trajectories in general brain size and cognition across YTO. Specifically, we predicted that GE individuals will demonstrate significantly larger brain volume (primary outcome measure) and stronger cognition scores (secondary outcome measures) prior to 20 YTO and significantly smaller brain volume and weaker cognition between 20−0 YTO. Using our updated recruitment target of 1,030 assessments across 450 participants, we estimated at least 90% power to reproduce our previous findings at p = .01 (except for cortical thickness; Table 5). Note that Table 5, which shows the results of our power analysis, includes functional and structural measures, but that our power analysis is primarily based on the structural findings from Kids-HD. Assuming 40% of participants are GE (as in the previous study), we can assume at least 400 visits from 180 unique genetically affected participants. The power analysis used the Kids-HD sample from Neema et al. (2024), and was based on 136 visits from 79 gene-expanded participants. Because the mean number of visits (and hence, statistical information) per participant will be higher in ChANGE-HD, a conservative estimate of the overall increase in statistical information (i.e., log-likelihood statistics) is obtained from the ratio of unique participants, which is 2.278. If the findings from Kids-HD hold, then the expected values of the analogous F statistics (Table 5) will increase by at least 2.278-fold. Standard power calculations using these projected F statistics yield results that exceed the above-claimed minimum statistical power.

**Table 5 pone.0336088.t005:** Tests used for hypotheses and power analysis (from Neema et al., 2024).

		Kids-HD				Change-HD		
**Measures**	**N**	**ndf**	**ddf**	**F**	**p**	**Projected F**	**Projected NCP**	**Power**
General Ability Index**	136	1	87.66	13.50	<0.001	30.78	29.445	0.997
Behavior composite**	135	2	120.27	10.91	<0.001	24.87	47.343	>0.999
PANESS**	128	1	46.12	8.92	0.005	20.34	18.933	0.956
Whole brain*	117	3	62.63	7.79	<0.001	17.76	49.491	>0.999
Cerebrum	117	3	62.55	7.80	<0.001	17.78	49.557	>0.999
Cortical gray matter*	117	1	99.90	12.22	<0.001	27.86	26.593	0.995
Cortical surface area	117	1	95.22	12.17	<0.001	27.75	26.468	0.994
Cortical thickness*	117	1	54.67	2.95	0.091	6.73	5.612	0.406

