
#### Statistical analysis using YTO Models.

We will employ a YTO model, which provides a more detailed representation of disease-related changes (between 50 and 0 YTO) than an age-based analysis [15,16,18,23]. Our statistical analyses are derived from Langbehn et al. [80] and our own work [17] investigating neural and behavioral changes across YTO. This method is based primarily on data from individuals with CAG repeats between 41 and 56 [80] but extrapolation has generalized usefully to CAG repeats extending beyond this range (40, 57–70, etc.) [17]. Because individuals with between 36–39 CAG repeats represent an incomplete penetrance group, they will be excluded from the YTO analysis and will be examined separately in exploratory analyses. Individuals with >70 CAG repeats will also be excluded as they are likely to have already begun showing motor symptoms of HD and are likely classified as patients with JOHD. All hypotheses relate to either systematic group difference between GE and GNE individuals or to differences within the GE group driven by CAG expansion length and age (or years to onset as in the NfL analysis). Our analysis approach will include the following steps: 1) age and sex correction based on the data from healthy controls, 2), estimation of YTO, and 3) YTO modeling with testing for potential additional sex differences and sex by YTO interactions.

For each dependent variable, we apply statistical corrections to separate developmental effects of typical aging from those experienced by GE individuals as part of the disease trajectory. We perform this correction by modeling age and sex effects in GNE controls using a regression that includes within-subject and within-family random effects. The models incorporate both linear and potential non-linear age relationships. Nonlinearity is modeled flexibly via restricted cubic splines (“natural splines”). The degree of non-linearity (up to five degrees of freedom) is determined by choosing the model with the lowest Akaike Information Criterion (AIC), with tied AIC values (≤ 1.0) favoring the simpler model. We also test the model for sex and sex-by-age interactions, which are excluded from the final model if found to be nonsignificant. The fitted values for this model are then subtracted from the dependent value to complete the correction.

Estimation of age of motor symptom onset is calculated using the Langbehn model [80] shown below:

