$$\begin{array}{c} Age\;of\;motor\;symptom\;onset=\text{2}\text{1}.\text{5}\text{4}-(\text{9}.\text{5}\text{5}\text{6}-\text{0}.\text{1}\text{4}\text{6}*CAG) \end{array}$$

YTO is then calculated by simply subtracting participants’ ages (in years) from age of motor symptom onset. (The abbreviation YTO, now established by precedent, stands for a slight misnomer. The value is the number of years from the mean age of onset for those with the given CAG length. It is not the individual’s number of years to onset—which is unknowable—and is slightly different from the individual’s expected years to onset, given that they have reached their current age without already experiencing onset.)

A limitation of this YTO approach is that it can only approximate the relationship between true years to HD onset and the outcome measures. As noted earlier, the YTO calculations are slightly biased estimates of participants’ expected years to onset. Furthermore, a person’s true years to onset has a probability distribution around the CAG-specific average. For concave relationships, such as those we typically expect in the neurodevelopment of brain volumes, substitution of an average value for a probability distribution causes at least slight underestimation of the predicted value that would be obtained from a model based on the true (but unknowable) number of years from onset (Jensen’s inequality).

We assess the relationship between YTO and age- and sex-adjusted outcome measures in GE individuals using an additional mixed effects regression, again including random effects for repeated measures of the same participant and for similarities between participants from the same family. Similar to the GNE model described above, the potentially nonlinear influence of YTO is modeled using restricted cubic splines with degrees-of-freedom chosen by AIC. Sex and sex interactions with YTO are tested and included in the model if significant. The mixed effect models are fitted by maximum likelihood and F-test degrees of freedom are estimated using the Satterthwaite approximation. The summary of the resulting model indicates a p-value for the effect of YTO, which, if significant, indicates a statistically meaningful difference of GE from GNE along the YTO trajectory. Finally, we plot these relationships and their 95% confidence intervals to determine where these differences occur along the trajectory (50−0 YTO)

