To assess the relationship between age- and sex-adjusted neuroimaging variables (e.g., cortical grey and white matter volume, striatal volume, corticostriatal structural and functional connectivity, etc.) and clinical outcomes in GE individuals, we apply modeling techniques as described above. The models include random effects of subject and family, but exclude age and sex, as the values will have already been corrected using the data from GNE participants. Imaging measures are generally predictor variables, and clinical measures are the outcomes, reflecting the potential causal relationships between the two measurement classes. As in our previous work [17], we also split our GE participants into two groups with a cutoff of 20 YTO and test for differences in the imaging versus clinical relationships. This is based empirically on our work [17] showing divergence in neural and behavioral measures at this point in the YTO trajectory and because of work showing an upward trend in NfL at 20 YTO [18]. As described above, potential non-linear relationships between biomarkers and clinical measures are interrogated using restricted cubic splines (up to five degrees of freedom). For all analyses, a *p* value of < 0.05 is considered statistically significant.

In addition to our hypothesis-driven analyses, we also plan to perform detailed exploratory analyses to uncover novel neuroimaging biomarkers that both distinguish GE and GNE individuals and individuals with variations in HD-related single nucleotide polymorphisms (SNPs). For example, machine learning approaches, such as deep learning, have been applied to neuroimaging data from patients with neurodegenerative disorders to identify how those SNPs affect brain anatomy and function [81]. As mentioned above, SNPs in several genes explain variation in the eventual onset of motor symptoms in HD [32–34]. Using deep learning and other machine learning approaches as exploratory tools may reveal new mechanistic information about how these SNPs shape neurodevelopment and -degeneration.

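### Subtracting the GNE age curve as if known and F-testing a YTO spline chosen by AIC as if pre-set makes p-values and 95% intervals too optimistic

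*Protocol article*

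**What the plan says.** The section on statistical analysis using YTO models describes two separate fits.

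- **Step 1, GNE only.** Age and sex effects are estimated in a mixed model. The age spline has up to five degrees of freedom (df), chosen by lowest AIC, with the simpler model preferred when AIC values lie within 1.0. Sex terms are dropped if not significant. Then "The fitted values for this model are then subtracted from the dependent value to complete the correction".
- **Step 2, GE only.** The corrected values are regressed on YTO, and "the potentially nonlinear influence of YTO is modeled using restricted cubic splines with degrees-of-freedom chosen by AIC". Sex terms are again kept only if significant. The F-test uses Satterthwaite df. The p-value is read from the summary of this fit, and a significant YTO effect is taken as a GE-GNE difference. Finally, "we plot these relationships and their 95% confidence intervals to determine where these differences occur along the trajectory".

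The threshold is general: "For all analyses, a *p* value of < 0.05 is considered statistically significant". The power section works at a stricter level: "we estimated at least 90% power to reproduce our previous findings at p = .01", with cortical thickness excepted. The limitations paragraph covers only YTO as a stand-in for true years to onset. It mentions neither first-step error nor spline selection.

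**The concern.** Two sources of uncertainty drop out of the reported inference.

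1. **The control curve is estimated.** YTO is predicted onset age minus current age, so an error in the GNE age curve enters the GE residuals as a function of age and shows up partly as a YTO trend. GNE is only 1.5 times the size of GE (270 against 180), so this error is not negligible.
2. **The YTO spline is picked because it fits.** Testing the chosen spline on its own df, as if it had been fixed beforehand, rejects too often. Table 5 lists numerator df of 1, 2, 3 or 5 depending on the outcome, which fits the reading that data-chosen df are then treated as given.

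Both errors run in the same direction. At stake are the false-positive rate of the YTO test and the placing of GE-GNE differences along 50-0 YTO. The Discussion would use reproduced early-life advantages to caution against early lowering of mutant huntingtin, so the reliability of those two results matters.

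**Working it through.** **Inputs from the article.** Size: "Using our updated recruitment target of 1,030 assessments across 450 participants". Group split: "Assuming 40% of participants are GE (as in the previous study), we can assume at least 400 visits from 180 unique genetically affected participants". That leaves 450 - 180 = 270 GNE participants and about 1,030 - 400 = 630 GNE visits. Ages run from 6 to 30.

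**The plan's own figure first.** The information ratio is "obtained from the ratio of unique participants, which is 2.278", and 180/79 = 2.278. For thalamus, projected F = 7.47 x 2.278 = 17.02 (Table 5: 17.03). The footnote formula with the Kids-HD ddf gives 17.03 - 2 x 17.03/102.87 - 1 = 15.70, close to the printed NCP of 15.871. Power is P(non-central chi-square(ndf, NCP) > 0.99 quantile of the central chi-square). With the printed NCPs:

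| Outcome | Table 5 | Recomputed |
|---|---|---|
| Thalamus | 0.916 | 0.920 |
| PANESS | 0.956 | 0.962 |
| Cortical gray matter | 0.995 | 0.995 |
| Cortical thickness | 0.406 | 0.418 |

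All rows of Table 5 agree within 2 points. The article gives no type I error or coverage for the two-step procedure, so these were simulated.

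**Null simulation.** GE and GNE share one age curve. Natural splines have 1-5 df, AIC is used with the 1.0 tie rule, and the F-test and pointwise intervals come from step 2. There were 6,000 replicates in each of six scenarios. The following are assumptions, not in the article:

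- CAG mean 44 with SD 2, 3 or 5
- subject plus family share of variance (ICC) 0.70-0.90
- 1-3 members per family
- linear or curved GNE age effect
- variance ratios known
- F denominator df set to GE participants minus 6, in place of Satterthwaite

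Onset age was taken as 21.54 + exp(9.556 - 0.146 x CAG). This gives 26.3 and 26.1 YTO for the article's two examples, which it states as 26. The equation as printed gives 11.0 and -3.7.

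| Procedure | Rejection at nominal 5% | 95% coverage |
|---|---|---|
| GNE curve known, YTO df fixed | 4.8-5.5% | about 95% |
| AIC selection only | 11.0-11.5% | 92-94% |
| Estimated GNE curve only | 6.2-9.0% | 88-94% |
| Both, as described | 13.7-17.3% | 86-91% |
| Joint model, pre-set df (age 3, YTO 3) | 4.7-5.3% | 94.2-95.5% |

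At nominal 1% the procedure as described rejects 3.4-5.5%; at nominal 0.1%, 0.3-0.9%. A separate set of runs (ICC 0.7-0.9, CAG SD 3-5) gave about 13-14% for the full procedure at nominal 5%, 9-10% for AIC alone, 5-7% for the GNE curve alone and 4-5% with neither. Taken together, the rejection rate at nominal 5% is about 13-17%, with about 9-12% from AIC alone and 5-9% from the GNE curve alone.

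**Effect on precision and power.** Ignoring first-step error, the true variance of the linear YTO slope is 1.13-1.35 times the reported one. Since 1/sqrt(1.13) = 0.94 and 1/sqrt(1.35) = 0.86, the standard error is understated by about 6-14%. Dividing the Table 5 NCPs by 1.1 to 1.4 at alpha 0.01 gives thalamus 0.89-0.79 and PANESS 0.94-0.87. Whole brain, cortical gray matter and cerebral white matter stay at 0.96 or above.

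**The case against.** - **A condensed article.** A fuller analysis plan could contain a bootstrap or a joint model. That is possible, but the article does say where the p-value and intervals come from, so the point concerns a stated rule and not an omission.
- **Extent.** A reader might infer that every headline result is unsafe. The figures do not support that. Standard errors are 6-14% too small from first-step error, coverage is 86-91%, and the volume outcomes with large projected F keep their power. The simulated rejection rate also counts any non-flat curve, including shapes that contradict the predicted pattern of larger before 20 YTO and smaller after. It is therefore not the rate of falsely confirming that hypothesis.
- **Group sizes.** The YTO analysis excludes CAG 36-39 and above 70, so the analysed GE group is smaller than 180 and the GNE group relatively larger. That reduces the weight of GNE-curve error. The article does not give the number excluded, and selection by AIC is unaffected by the ratio.
- **Siblings.** It is tempting to add that separate family effects in each group ignore the correlation between GE and GNE siblings and so make matters worse. This probably works the other way, because positive sibling covariance reduces the variance of a GE-minus-GNE difference. With two siblings per family and total ICC 0.9 (assumed), the ratio of true to reported slope variance fell from 1.29 with no family component to 1.21 and 1.17 with family shares of 0.30 and 0.45. It is not a cause of optimism here.
- **Fixed df have a price.** This stands. At the Table 5 NCPs and alpha 0.01, a 3-df test takes thalamus from 0.92 to 0.81 and PANESS from 0.96 to 0.89. Table 5 also shows 5 df for striatum and globus pallidus, which 3 df might not follow.

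**Conclusion.** The point holds in direction and is material in size. As written, the analysis rejects about 13-17% of the time at nominal 5% and about 3-5.5% at nominal 1% when GE and GNE do not differ, and its pointwise 95% intervals cover about 86-91%. Choosing the YTO spline by AIC contributes more than the estimated control curve. Results near 0.05 and the reading of where the curves separate along 50-0 YTO are the ones at risk. Clear results for whole brain, cortical gray matter and cerebral white matter are little affected, and cortical thickness was already excepted from the power claim.

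The ranges rest on the assumed CAG spread, variance shares and family sizes. Selection of sex terms by significance was not simulated and could add some inflation.

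**What to change.** **Option 1: keep the two-step form, which preserves comparison with Kids-HD.** Obtain p-values and intervals by resampling whole families, GE and GNE members together, through both steps. Repeat the AIC choice and the sex-term selection in each resample. For p-values, resample under a null of no GE-GNE difference.

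**Option 2: one joint mixed model.** Fit GE and GNE together with a shared age spline, sex, a GE indicator, a GE x YTO spline, and subject and family random effects spanning both groups. Pre-set the YTO df for each outcome, for example from the Kids-HD numerator df in Table 5, and do not impose 3 df throughout.

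**Cost.** More programming and wider intervals in either case. Option 2 also loses some power wherever the pre-set df exceed what the curve needs, so Table 5 should be restated if the df change. Option 1 keeps the adaptive curve and needs no new df.

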***HTT* impacts brain structure and function along the entire spectrum of repeats**: Higher repeats are associated with better cognitive skill and greater brain volume in GE and GNE individuals [13,14].**Methodological challenges of modeling age and CAG separately, versus years-to-onset model (which incorporates both):** The Kids-HD study employed an accelerated longitudinal design (ALD), the gold standard for evaluating brain development in children, which combines cross-sectional and longitudinal data to model age-related changes across a broad developmental window. This model showed not only interesting findings of accelerated striatal development, where GE children reached peak striatal volume years before the GNE group, but that these trajectories were profoundly affected by CAG repeat length [15]. We also found that every CAG repeat conferred a greater advantage in general cognitive ability [14]. This effect peaked at repeats of 43 and individuals with longer CAG repeats showed trajectories that were declining in function after age 15, likely representing changes due to the degenerative phase of the disease. The age-trajectory modeling results highlighted the profound consequences *HTT* and CAG repeat-length has on neurodevelopment. These findings recapitulate the well-established negative relationship between CAG repeat length and age of motor onset and require an updated model to take both factors, and their interactions, into account. Given the influence CAG repeats and age exert on longitudinal brain development, we began modeling the data in a Years-To-Onset (YTO) fashion to evaluate the time course of the disease from development to degeneration. The YTO model predicts the age of motor onset based on the participant’s current age and CAG repeat length. Importantly, the YTO model can reveal information about disease trajectory that is obscured when plotting data by age. For example, Reasoner et al. (2022) found that cortical volumes are similar across age groups [16], while Neema et al. (2024) found evidence for higher and lower cortical volumes depending on the YTO of the individual [17]. The critical difference between approaches is that while higher age and lower YTO both predict decline in cognitive and motoric function, age-only models ignore variability in disease trajectory caused by CAG repeat length. An example of the difference between an age-only trajectory and a YTO model is as follows: An 8-year-old with a CAG repeat length of 48 and a 22-year-old with a CAG length of 43 both have 26 YTO, despite being on opposite ends of the age trajectory model. Thus, potential differences in cortical volumes could have been missed by Reasoner et al. (2022) because participants at similar ages were at different points in their disease trajectory. Additionally, when evaluating a biomarker of degeneration in Kids-HD (neurofilament light; “NfL”), we found that NfL levels are normal as far back as 40 YTO but rise around 20 YTO [18]. These findings support the notion that the YTO model can accurately characterize the developmental phase of the disease process, which occurs 20 years before the onset of motor symptoms.**The antagonistic pleiotropy theory of *HTT* and its implications for neurodevelopment:** In our most recent publication, we revealed that GE individuals from 50−20 YTO have larger cerebral volumes, more cortical surface area, and higher IQs compared to GNE subjects, but the opposite is true after 20 YTO [17]. Striatal and pallidal volumes remain comparable in volume to GNE until 20 YTO after which they dramatically decline in volume, consistent with early vulnerability of the basal nuclei. These findings challenge the traditional concept of HD as a uniquely neurodegenerative disorder and highlight the neurodevelopmental role of *mHTT.* Additionally, Kids-HD research uncovered potential early advantages of *mHTT* in GE children, such as larger brain development that supports enhanced cognitive development and reduced depression/anxiety. However, these children will indeed develop HD, highlighting the yoking of advantage with disadvantage. Our findings support the notion of antagonistic pleiotropy in HD, where the same neurodevelopmental differences that confer early advantage eventually lead to vulnerability and subsequent degeneration [19]. Collectively, they reshape our understanding of the evolutionary implications of *mHTT* and its potential role in brain development

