Be diagnosed with JOHD by a trained neurologist prior to the age of 21, based on motor symptomology (the participant’s genetic status is confirmed after consent is obtained).Be between 6–30 years old at baseline. Thus, even though the diagnosis is made prior to 21, assessment for the study is not restricted to ages under 21.Not be bed-ridden, unable to communicate, or beyond travel conditions that are too strenuous for the individual.

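### The printed age-at-onset equation lacks its exponential, has the wrong sign, and cannot reproduce the protocol's own 26-YTO example

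*Protocol article*

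**What the plan says.** In the protocol article, the section on statistical analysis using YTO models gives a single equation for the age of motor onset. In plain notation it reads onset = 21.54 − (9.556 − 0.146 × CAG). The next sentence defines the predictor: "YTO is then calculated by simply subtracting" each participant's current age from this onset age.

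The same section limits who enters this analysis. At the lower end, "individuals with between 36–39 CAG repeats represent an incomplete penetrance group, they will be excluded from the YTO analysis"; at the upper end, "Individuals with >70 CAG repeats will also be excluded". That leaves CAG 40 to 70. The Participants section sets the age range at 6 to 30 years.

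Two statements in the Introduction (Lessons from Kids-HD) bear directly on the equation. One refers to the "well-established negative relationship between CAG repeat length and age of motor onset". The other is a worked example: "An 8-year-old with a CAG repeat length of 48 and a 22-year-old with a CAG length of 43 both have 26 YTO".

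The power section predicts larger brain volume and better cognition in GE participants before 20 YTO and the reverse from 20 to 0 YTO. The analysis section plots trajectories from 50 to 0 YTO and splits GE participants at 20 YTO.

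**The concern.** The printed equation is linear in CAG. Once the bracket is opened, the CAG coefficient is positive, so more repeats mean later onset. That contradicts the direction stated in the Introduction. A slope of 0.146 years per repeat also looks too shallow to produce a 50-year YTO scale in people aged 6 to 30.

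YTO is the key predictor in the GE trajectory models that test the central hypothesis, and it defines the 20-YTO split used in the imaging-versus-clinical models. Anyone who codes or replicates the analysis from this line would get a predictor with a reversed CAG effect and a range that misses the region where the main hypothesis applies.

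**Working it through.** **Inputs.** The onset equation, the YTO definition and the CAG limits (40 to 70) come from the YTO-model section. Ages 6 to 30 come from Participants. The example (age 8, CAG 48; age 22, CAG 43; both 26 YTO) and the negative CAG relationship come from Lessons from Kids-HD.

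**1. Simplify the printed equation.** 21.54 − (9.556 − 0.146 × CAG) = 11.984 + 0.146 × CAG. Onset rises by 0.146 years per repeat.

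**2. Try to reproduce the protocol's example.**
- CAG 48: 11.984 + 7.008 = 18.99; minus age 8 gives **10.99** YTO (stated: 26).
- CAG 43: 11.984 + 6.278 = 18.26; minus age 22 gives **−3.74** YTO (stated: 26).

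The example is not reproduced, and the two people are not even equal to each other.

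**3. Try the near variants with the same constants.**

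| Form of onset equation | Age 8, CAG 48 | Age 22, CAG 43 |
|---|---|---|
| 21.54 − (9.556 − 0.146 × CAG), as printed | 10.99 | −3.74 |
| 21.54 − exp(9.556 − 0.146 × CAG) | 0.76 | −26.98 |
| 21.54 + (9.556 − 0.146 × CAG) | 16.09 | 2.82 |
| 21.54 + exp(9.556 − 0.146 × CAG) | **26.32** | **26.06** |

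Only the last form rounds to 26 for both. For CAG 48, exp(9.556 − 7.008) = exp(2.548) = 12.78, so onset is 34.32. For CAG 43, exp(9.556 − 6.278) = exp(3.278) = 26.52, so onset is 48.06. Two corrections are needed. Restoring the exponential alone still leaves onset rising with CAG, because the reversal comes from the minus sign before the bracket.

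**4. Compare onset ages (years) across the analysed CAG range.**

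| CAG | Printed | 21.54 + exp(…) | Difference |
|---|---|---|---|
| 40 | 17.82 | 62.64 | 44.82 |
| 43 | 18.26 | 48.06 | 29.80 |
| 48 | 18.99 | 34.32 | 15.33 |
| 56 | 20.16 | 25.51 | 5.35 |
| 70 | 22.20 | 22.05 | −0.15 |

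The error is not a constant shift, so re-centring YTO would not repair it. Within the analysed range the printed onset never exceeds 22.2 years, whereas the section on the juvenile-onset study puts typical adult onset at 40 to 50.

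**5. Check the reachable YTO range.** The grid is whole-year ages 6 to 30 by CAG 40 to 70, which is 25 × 31 = 775 combinations. It shows which values are possible, not how many participants will have them.
- As printed, the maximum is 22.20 − 6 = **16.2** YTO (age 6, CAG 70) and the minimum is 17.82 − 30 = −12.2. No combination reaches 20 YTO, and 325 are negative. Reaching 20 YTO at age 6 needs onset at 26, so CAG = (26 − 11.984) / 0.146 = 96, well above the limit of 70.
- With 21.54 + exp(…), YTO runs from 56.6 to −7.9. Of the 775 combinations, 181 fall in 50 to 20 YTO, 463 from 0 to below 20, 122 are negative and 9 exceed 50.

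**The case against.** The strongest reply is that this is a printing error and not a flaw in the analysis. The protocol names the onset model and cites its source. Its worked example agrees with the exponential form to rounding, and the 50-to-0 scale with a 20-YTO cutoff could not have come from the printed line. An analyst who coded that line literally would soon notice that no YTO exceeded 16.2. This stands as far as it goes: the study's code is probably right, and the harm described here depends on literal use of the equation. It does not remove the need for correction, because no other place in the article prints a correct version.

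A second reply is that machine reading of the PDF may have dropped the exponential. That cannot be wholly excluded. However, the equation is otherwise intact, and a lost exponential would not turn a plus into a minus.

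A third point is that the exponential form is an inference, since it is printed nowhere in the article and rests on two values rounded to whole years. That is fair, and it is why the correction should be checked against the cited source.

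The scope also needs stating with care. YTO is not the only predictor in every model: sex terms may be retained, and imaging measures are generally the predictors in the imaging-versus-clinical models. YTO also still falls with age as printed; it is the CAG effect that is reversed.

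**Conclusion.** The equation is wrong as written, and the article's own figures show it. It reverses the stated CAG effect, misses the worked example by about 15 years for one participant (26 against 10.99) and about 30 for the other (26 against −3.74), and caps YTO at 16.2 for eligible participants. If it were used literally, the region before 20 YTO would be empty, the 20-YTO split would yield one group, and everyone older than 22.2 years would have negative YTO whatever their CAG length.

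These results rest on the stated limits (ages 6 to 30, CAG 40 to 70) and on the equation having been transcribed faithfully. They do not show that the study's analysis code is wrong; the worked example suggests otherwise. Because this is the only printed definition of the key predictor, it must be corrected before analysis.

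**What to change.** Replace the equation with the form that is consistent with the worked example, onset = 21.54 + exp(9.556 − 0.146 × CAG), after confirming it against the cited source of the onset model. Both changes are required: the exponential and the plus sign.

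Add a sentence requiring the analysis code to reproduce the example before the data are analysed: onset at 34.3 years for CAG 48 and 48.1 years for CAG 43, and about 26 YTO for both participants.

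The cost is one corrected line and one code check. Design, sample size and data collection are unaffected.
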